### Statistical analysis

We estimated that a total of 400 newborns can be included within a period of three years. In a previous study of the CDH study group, the incidence of BPD and/or death within the first 28 days of life is reported to be about 50% [9]. Assuming a difference of 15% in BPD and/or death within the first 28 days between both treatment groups, 186 patients are required per arm for a power of 80% at two-sided alpha is 0.05. To allow for some non-evaluable patients and dropouts, 200 patients per group will be included. To achieve equal distribution of the two ventilation modes among the participants, block randomization stratified per centre will be carried out. The data-analysis will be carried out at the Erasmus MC, Rotterdam. An intention-to-treat analysis will be performed. A p-value (two-sided) < 0.05 will be considered significant in all analyses.

The primary endpoint will be evaluated using multiple logistic regression analysis taking account of: centre, lung-to-head ratio, position of the liver (intra-abdominal or intra-thoracic) and the side of the defect (left, right or central). A subgroup analysis will be carried out in operated infants to evaluate the defect size, according to the CDH study group defect size scale (http://www.cdhsg.net).

The secondary endpoints will be evaluated by using the following statistical tests. Overall mortality in the first year of life will be analysed by Kaplan-Meier curves and Log rank tests. The chi-square test will be used to analyse number of treatment failures, presence of pulmonary hypertension according to echocardiographic parameters, requirement of medication at discharge and during the first year of life, and need for ECMO therapy (in ECMO centres). The Mann-Whitney test is used to evaluate the severity of chronic lung disease, number of days on the ventilator and the fraction of days with required medical treatment for pulmonary hypertension during the hospital admission. In the evaluation of the severity of chronic lung disease and the number of days on the ventilator, deaths are counted as worst outcome according to the intention-to-treat principle. Repeated measures ANOVA is used to evaluate levels of laboratory markers for ventilator-induced lung injury or pulmonary hypertension and pulmonary function at the age of six and twelve months. This analysis allows for missing data at different time points and is considered as the optimal way for evaluation of longitudinal data.

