### Laboratory analyses

During the study, blood, urine and tracheal samples are collected. Separate parental informed consent is asked for taking, analysing and storing these samples.

Blood, urine and tracheal samples are taken within the first 2 hours of life and on days 3, 7, 14 and 28. Blood sampling is only done if a central or peripheral line is present and in combination with routine laboratory measurements. Urine sampling is only done if the patient has a urine catheter. Sampling of tracheal aspirates is only done during routine suctioning. In that way, sampling of laboratory markers are of minimal burden for the patient.

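### Repeated measures ANOVA is justified by a tolerance of missing data that its classical form lacks and that a mixed model has only under an unstated assumption

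*Protocol article*

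**What the plan says.** The protocol article, under Statistical analysis, states: "Repeated measures ANOVA is used to evaluate levels of laboratory markers for ventilator-induced lung injury or pulmonary hypertension and pulmonary function" (lung function being measured at six and twelve months). The next sentence gives the reason: "This analysis allows for missing data at different time points and is considered as the optimal way for evaluation of longitudinal data". No model form, estimation method or covariance structure is given, and no restriction to complete cases is stated.

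Under Laboratory analyses the schedule has five time points: "Blood, urine and tracheal samples are taken within the first 2 hours of life and on days 3, 7, 14 and 28". Each specimen carries a condition:

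- Blood: "Blood sampling is only done if a central or peripheral line is present and in combination with routine laboratory measurements".
- Urine: "Urine sampling is only done if the patient has a urine catheter".
- Tracheal aspirate: "Sampling of tracheal aspirates is only done during routine suctioning".

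The same section asks for separate parental consent for samples. Under Study procedures, observation ends at day 60 or at discharge if that is earlier. Under Statistical analysis, deaths are ranked as the worst outcome for severity of chronic lung disease and for ventilator days. No corresponding rule is given for the markers.

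**The concern.** The protocol gives a reason for its choice of method, and that reason fails for the method as ordinarily understood. Classical repeated measures ANOVA works on a full set of measurements per subject. Standard routines either drop a subject with a gap or refuse the data.

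This matters because the design builds in gaps. An infant who improves loses the line, the catheter and the tube, and an infant who dies is no longer sampled. A complete-case set would therefore consist mainly of survivors who still have a line or catheter, or still need suctioning, at day 28. Death and days on the ventilator are themselves outcomes compared between the arms, so the chance of being sampled may depend on the allocated mode. If it does, the sampled infants are no longer comparable by randomisation.

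What is at stake is the secondary aim of comparing ventilator-induced lung injury and pulmonary hypertension through laboratory parameters.

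**Working it through.** **The plan's own figure.** The only calculated figure in the article is the 186 per arm for the primary endpoint. It reproduces closely with a continuity correction (183 for 50% against 35%; 187 for 57.5% against 42.5%) and has no bearing on this point. No figure is given for the marker analysis.

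**Inputs from the article.** Five sampling times; at most 400 infants, fewer if some parents decline the separate sample consent.

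**Assumed input.** Availability per visit, *q*. The article gives none, so a range is shown, with visits taken as independent.

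**Formulas.** Infants with all five samples = 400 × *q*⁵. Records available to a mixed model = 400 × 5 × *q*. Share of infants with at least one sample = 1 − (1 − *q*)⁵.

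| *q* | *q*⁵ | Infants with all five | Records available (of 2000) | At least one sample |
|---|---|---|---|---|
| 0.95 | 0.774 | 310 | 1900 | >99.9% |
| 0.90 | 0.590 | 236 | 1800 | >99.9% |
| 0.80 | 0.328 | 131 | 1600 | >99.9% |
| 0.70 | 0.168 | 67 | 1400 | 99.8% |
| 0.50 | 0.031 | 13 | 1000 | 96.9% |

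**If sampling stops and does not resume.** Independence is only one pattern. With monotone loss, the number of complete infants is simply the day-28 availability times 400. An assumed sequence of 95, 90, 75, 50 and 30% gives 0.30 × 400 = 120 complete infants. They contribute 5 × 120 = 600 of 400 × (0.95 + 0.90 + 0.75 + 0.50 + 0.30) = 1360 records, or 44%. A milder sequence of 95, 90, 80, 65 and 50% gives 200 infants and 1000 of 1520 records, or 66%.

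**Direct check of the stated property.** One data set was simulated with 400 infants, five times and 70% availability at random. A classical repeated measures ANOVA routine rejected it as unbalanced; only 65 infants had all five samples. A linear mixed model on the same data used 1399 records from 399 infants. So the property fails for the classical form and holds for the mixed-model form.

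**What the mixed model still needs.** In the simulation, missingness was unrelated to anything. In the trial it follows line or catheter removal, extubation, discharge and death. A likelihood-based model is valid only if, given arm, centre and the marker values already observed, the chance of a missing sample does not depend on the unseen value. Removal of support because the infant has improved may break that condition. After death the marker level does not exist, and the model would still estimate a mean as if it did.

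**The first sample.** It is scheduled within two hours of birth. Under Study procedures, allocated ventilation must start within the same two hours, so the sample may come after treatment has begun. The abstract places it more loosely, on the first day of life. Urine is drawn from an eight-hour collection, which cannot be complete within two hours of birth.

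**The case against.** The strongest reply is that the two sentences should be read together. Repeated measures ANOVA is also used as a name for mixed-model analysis of repeated measures, and the sentence on missing data suggests that this was meant. Model type and covariance structure are details that a condensed article may leave to an analysis plan that is not shown. This stands in part: a mixed model may well be intended, and the absence of model details is no fault here. But the missing-data sentence is a positive statement. Under one reading it is wrong; under the other it is true only with an assumption that the sampling rules put in doubt.

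Three stronger readings are tempting and not supported:

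- A reader might infer that the plan analyses only infants sampled at every time point. The text sets no such rule and says that gaps are allowed. The complete-case loss is what follows if the named method is run in its classical form.
- A reader might infer a definite loss of power. Every availability rate is assumed. Setting a complete-case test against a comparison at one early day would also compare two different questions, not two methods for the same one.
- A reader might infer that extubation and death differ by arm. That is what the trial is testing, and the Discussion says that no specific conclusion on either mode can yet be drawn. Dependence on arm is possible, not established.

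**Conclusion.** The point holds as a mismatch between a named method and its stated justification. The justification fails for classical repeated measures ANOVA. For a likelihood-based mixed model it holds only under missing at random, which is not stated and is doubtful where sampling stops with recovery or death. The missing rule for deaths among the markers adds to this.

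The size is not computable from the documents. The table shows what a complete-case analysis would cost under assumed, independent availability, with 400 infants as an upper limit; the gaps in the trial will be linked to severity and may differ by arm.

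The primary endpoint, its logistic regression, the sample size, mortality, severity of chronic lung disease and ventilator days are unaffected. This is a moderate correction to the analysis of secondary endpoints. It should be settled before analysis, so that the reading of the method is not chosen after results are seen.

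**What to change.** 1. Replace repeated measures ANOVA with a likelihood-based linear mixed model with treatment, time, treatment-by-time and centre, using all available samples. For lung function, which the Follow-up section analyses separately in the two centres, the centre term drops out.
2. Replace the sentence on missing data with the missing-at-random assumption that the model needs.
3. Interpret later time points as conditional on being alive and sampled. Report by arm, at each time, the numbers sampled, no longer sampled (with the reason) and dead.
4. Do not treat the first sample as a pre-treatment baseline unless it was taken before allocated ventilation started.

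The change is to wording. Sample size and sampling schedule stay as they are; the counts need the reason for each missing sample and the time of the first sample relative to the start of ventilation, if these are not already recorded. The cost is that late marker comparisons become supportive, because they describe a selected group of infants.

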### Study procedures

Parental informed consent will be obtained antenatally to enhance quick randomization. Following antenatal diagnosis, the parents are to be counselled and will receive information about the study, including a patient information letter and an informed consent form. If both parents decide to participate in the study, as soon as possible after birth central randomization will take place by the treating physician using a website. This way concealed allocation is guaranteed. Within two hours after delivery, the allocated ventilatory treatment has to be started.

The patient receives the allocated ventilation treatment during the entire admission period on the intensive care unit. During surgery, the child preferably remains on the allocated ventilation type, provided the treating surgeon agrees. Should the surgeon opt for the other ventilation mode, the patient is switched to the allocated ventilation treatment again after surgery. If the patient has to be re-intubated within the first 60 days after the start of the allocated treatment, the patient receives the allocated treatment again. Patients are observed up to day 60 after birth or until discharge whichever comes first. In Figure 1, an overview of the study procedures is given.

**Figure 1 F1:**

**Overview study procedures**.

### Standardized treatment and ventilation settings

All infants participating in the VICI-trial are treated according to the same standardized treatment protocol which has been published recently [4]. This protocol of standard practice was decided upon available evidence and consensus between the participating centres.

After birth, all infants are immediately intubated. In general, our goals are to achieve preductal saturations between 85 and 95%, postductal saturation levels above 70% and arterial CO_2 _levels between 45-60 mm Hg (permissive hypercapnia). Conventional mechanical ventilation is provided by a neonatal ventilator capable of positive pressure ventilation or triggered modes (Babylog ventilator, Dräger Medical, Germany). High frequency oscillatory ventilation (HFO) is provided by a high frequency oscillatory ventilator (Sensormedics 3100A/B HFO Ventilator, Viasys Healthcare, USA).

If the allocated treatment is conventional ventilation, the following settings are used: a peak inspiratory pressure (PIP) of 20-25 cm H_2_O, a positive end-expiratory pressure (PEEP) of 2-5 cm H_2_O and a frequency of 40-60 per minute. In case of HFO, the settings are: a mean airway pressure (MAP) of 13 to 17 cm H_2_O, a frequency of 10 Hz, an amplitude (Δp, cm H_2_O) of 30 to 50 obtaining chest vibrations, and an inspiration/expiration rate (I:E) of 1:1.

According to our standardized treatment protocol, a chest radiograph is made as soon as possible after birth to assess the initial condition and is repeated guided on the patient's condition. In case of HFOV, a chest radiograph is also made after this ventilation mode is started to confirm that the lungs are not overinflated, as defined by a contralateral lung expansion of over 8 ribs. Also, echocardiography is performed within the first 24 hours after birth to assess pulmonary arterial diameter and right heart function. In all patients, a chest radiograph and echocardiography are repeated at day 28.

Weaning from conventional ventilation is done by means of decreasing PIP. Frequency and/or the PIP-PEEP were modified to achieve PaCO_2 _levels above 45 mmHg. In case of HFOV, Δp was decreased if the paCO_2 _was below 45 mmHg and FiO_2 _was decreased if preductal saturation levels were above 95%.

In case of hypovolemia and/or cardiogenic shock, saline fluid therapy is started (10 to 20 ml/kg of NaCl 0.9% up to three times during the first one to two hours), which is followed by inotropic therapy if necessary. At an oxygenation index of 20 or higher and/or a pre- and postductal saturation difference of 10% or more, 10-20 ppm iNO is given for at least one hour. Intravenous prostacyclin or prostaglandin E1 may be considered in case of no response to iNO. Sildenafil may be considered in the chronic phase of pulmonary hypertension.

Surgery is performed if the patient is physiologically stabile according to the criteria described in our protocol [4]. No routine paralysis is used.

### Treatment failure

In case of one or more failure criteria, the allocated ventilatory treatment may be switched. Also, an ECMO procedure may be started in centres where ECMO is available. After the ECMO-procedure has ended, the patient preferably receives the initial allocated ventilation mode. Because an intention-to-treat analysis will be performed, data from these patients are stored and analysed the same way as data from patients in whom no switching of ventilation mode or ECMO procedure took place.

The following failure criteria are applicable to the study patients:

• Inability to maintain preductal saturations above 85% (± 7 kPa or 52 mmHg) or postductal saturations above 70% (± 5.3 kPa or 40 mmHg)

• Increase in CO_2 _> 65 torr or mmHg (8.5 kPa) despite optimalization of ventilatory management

• PIP > 28 cm H_2_O or MAP > 17 cm H_2_O

• Inadequate oxygen delivery with metabolic acidosis defined as lactate ≥ 5 mmol/l and pH < 7.20

• Hypotension resistant to fluid therapy and adequate inotropic support, resulting in a urine output < 0.5 ml/kg/hour

• Oxygenation index consistently ≥ 40

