### Outcome measures

The primary outcome measure is BPD and/or death within the first 28 days of life. Secondary outcome parameters are overall mortality, severity of BPD, number of days on the ventilator, number of treatment failures, ventilation-induced lung injury and pulmonary hypertension according to clinical and laboratory parameters and need for ECMO (only for ECMO centres). BPD is defined as oxygen dependency at day 28, according to the definition of Jobe and Bancalari [27]. The severity of BPD is also defined according to this definition (see table 1).

**Table 1 T1:** definition of BPD according to Jobe and Bancalari

Gestational age	< 32 weeks	> 32 weeks
**Time point assessment**	36 wks PMA* or DC** to home, whichever comes first	> 28 days but < 56 days of life or discharge to home, whichever comes first

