All the above-mentioned analyses will allow for centre by stratification.

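### The CO2 treatment-failure limit is given as 65 mmHg and as 8.5 kPa, but 65 mmHg is 8.67 kPa and 8.5 kPa is 63.8 mmHg

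*Protocol article*

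**What the plan says.** The section Treatment failure lists six bulleted criteria. The CO2 criterion is a rise above "65 torr or mmHg (8.5 kPa) despite optimalization of ventilatory management". Nothing marks the kPa figure as approximate. The saturation criterion in the same list does mark its conversions that way, for example "preductal saturations above 85% (± 7 kPa or 52 mmHg".

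The consequence is stated at the head of that section: "In case of one or more failure criteria, the allocated ventilatory treatment may be switched". ECMO may also be started in centres that have it.

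Elsewhere the article gives CO2 in mmHg only. Standardized treatment and ventilation settings puts the goal at "levels between 45-60 mm Hg (permissive hypercapnia", and the weaning rules there use 45 mmHg twice. No other section restates the failure limit or says which unit governs.

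The section Outcome measures names "number of treatment failures" as a secondary outcome, and Statistical analysis assigns it a chi-square test.

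**The concern.** A threshold printed in two units should be the same threshold in both. Here a CO2 between about 63.8 and 65 mmHg exceeds the limit when read in kPa and does not when read in mmHg.

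The line is an operating rule, which is why it deserves more than a proofreading mark. Meeting any one criterion allows the clinician to leave the allocated mode, so the limit influences crossover and presumably the count of treatment failures. The trial runs in several European centres, and printing both units suggests that either may be read at the bedside. Centres that differ in the unit they use would then apply slightly different rules under one protocol.

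**Working it through.** **Inputs**

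- Conversion: 1 mmHg = 0.133322 kPa. Torr and mmHg are the same for this purpose.
- CO2 failure limit: 65 mmHg and 8.5 kPa (Treatment failure).
- Comparison pairs from the same list: 52 mmHg with 7 kPa, and 40 mmHg with 5.3 kPa.
- Upper end of the CO2 goal: 60 mmHg (Standardized treatment and ventilation settings).

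**Step 1: try to reproduce the printed 8.5 kPa**

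- 65 × 0.133322 = 8.666 kPa, which is 8.7 to one decimal.
- With the rounded factor, 65 / 7.5 = 8.667 kPa, the same result.
- Rounding to the nearest half kPa does give 8.5, but the list does not follow that rule, since it prints 5.3 kPa.

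The printed figure is therefore not reproduced.

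**Step 2: convert back and size the gap**

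- 8.5 / 0.133322 = 63.76 mmHg.
- Gap in mmHg: 65 − 63.76 = 1.24 mmHg.
- Gap in kPa: 8.666 − 8.5 = 0.166 kPa.
- Relative to the limit: 1.24 / 65 = 1.9%.
- Distance from the top of the goal range to failure: 65 − 60 = 5 mmHg by one figure and 63.76 − 60 = 3.76 mmHg by the other, a reduction of 1.24 / 5, about a quarter.

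**Step 3: compare with the other pairs in the list**

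| Printed mmHg | Converted to kPa | Printed kPa | Difference (kPa) | Marked approximate |
|---|---|---|---|---|
| 52 | 6.93 | 7 | 0.07 | yes |
| 40 | 5.33 | 5.3 | 0.03 | yes |
| 65 | 8.67 | 8.5 | 0.17 | no |

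The first two agree at the precision at which each kPa value is printed. The CO2 pair does not, and it is the one printed as exact.

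**Step 4: check the replacement**

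8.7 / 0.133322 = 65.26 mmHg, which is 0.26 mmHg from 65.

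**Step 5: who could be affected**

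Three conditions must hold together: the centre applies the kPa figure, the infant's CO2 stays between 63.8 and 65 mmHg despite optimised ventilation, and none of the other five bulleted criteria is met. The article gives no data from which to count such infants, so no number is offered.

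**The case against.** The strongest reply is that this is editorial. The leading figure is 65 mmHg, the kPa value is a bracketed conversion, and every other CO2 value is in mmHg, so a careful reader would apply 65 mmHg. That is a fair reading, and the fix adopts it. It does not make the bracket right, and a clinician whose blood-gas report is in kPa would have reason to use the bracket.

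The list also mixes precision, with a whole number in one place and one decimal in another, so a coarse conversion might be expected. This softens the contrast with the other pairs but does not remove it: the CO2 bracket is off by 0.17 kPa, against 0.07 kPa for the coarser of the other two.

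The remaining points concern consequence, and they largely stand:

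- Nothing says that any centre works in kPa.
- The criterion depends on a judgement that ventilation has been optimised, and switching is optional. A gap of 1.24 mmHg is small beside that discretion.
- Infants who switch or receive ECMO are analysed by intention to treat.
- The design has "block randomization stratified per centre will be carried out", and for the analysis "All the above-mentioned analyses will allow for centre by stratification". A unit difference between centres would apply the same limit to both arms within a centre.
- The article does not say whether a treatment failure is a criterion met or an actual switch. If only switches count, the effect on that outcome is smaller still.

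These points fix the severity at minor. They do not remove the error, which is a wrong number in a stated decision rule and not a detail left to a fuller document.

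**Conclusion.** The concern holds, as a minor error. The bracketed kPa figure does not match the mmHg limit beside it; the mismatch is 1.24 mmHg, or 1.9%. The arithmetic needs no assumption beyond the standard conversion.

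That 65 mmHg is the intended value is an inference from its leading position and from the mmHg-only CO2 values elsewhere. Any practical effect assumes that at least one centre applies the kPa figure. In that case the effect is at most slight non-differential noise in the failure count and in crossover. No between-arm bias follows from this alone. The primary endpoint, BPD and/or death within 28 days, does not use this limit.

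**What to change.** Replace 8.5 kPa with 8.7 kPa in the CO2 failure criterion and state that 65 mmHg governs. If the sponsor in fact meant 8.5 kPa, correct the mmHg figure to 64 instead; either way one of the two numbers has to change. Apply the single confirmed value wherever treatment failures are derived from recorded CO2.

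The cost is one corrected figure and a short note to the centres. Sample size, schedule and the primary analysis are unaffected.
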